### 2.2. Participants and Eligibility Criteria 

Participants were recruited from the general population by local advertisements. The participants of this study were asymptomatic adults, aged 18 to 49 years, of both genders, not reporting the presence of pain symptoms the previous 6 months before the study. Volunteers were contacted by email, and those who meet the eligibility criteria were included. All subjects signed a written informed consent before collecting any data.

Participants were excluded if the following were present: 1, belonephobia (fear of needle), 2, neurological, cardiovascular, or metabolic diseases; 3, any medical conditions causing pain; 4, cutaneous alterations; 5, pregnancy; 6, cognitive or sensitivity disorders; 7, fibromyalgia syndrome; 8, frequent/regular consumption of alcohol and other drugs; 9, had received any medication or physical therapy treatment the previous week; 10, intake of caffeine in the two hours prior to measurement; or, 11, vigorous physical activity on the day of testing.

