### 2.4. Outcomes

All outcomes were evaluated before (2 min) and immediately after (2 min) the intervention by an assessor blinded to the treatment allocation group. The experiment always took place in the same quiet room with a similar temperature and schedule for all participants. Before the baseline outcomes, the following socio-demographic variables were assessed: age (years), gender (male or female), weight (kg), height (m), body mass index (BMI) (kg/m^2^), smoking (yes or no), and level of physical activity (measured by the short version of the International Physical Activity Questionnaire (IPAQ-SF)) [30]. The order of outcome assessment was always the same: widespread PPTs, CPM and TS.

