### 2.6. Allocation and Randomization 

Participants were randomly assigned into one of four intervention groups: control group (no intervention), needling group (receiving a needling intervention but not electrical current), low-intensity percutaneous electrolysis group (receiving percutaneous electrolysis with low intensity of electrical current), and high-intensity percutaneous electrolysis (receiving percutaneous electrolysis with a high intensity of electrical current). 

Concealed allocation was conducted with a computer-generated randomized table of numbers created by an external statistician not involved in the analysis or interpretation of the results. Individual and sequentially numbered index cards with random assignment were prepared. The index cards were placed in sealed opaque envelopes, which were opened by an external assessor. Treatment allocation was revealed to the participants after collection of baseline outcomes. 

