### 2.8. Statistical Methods 

Data were analyzed by using the IBM-SPSS software package (version 26.0). The significance threshold was established at 0.05 and the limits of the confidence interval at 95%. Changes in outcomes were tested on the basis of the intention-to-treat principle. Firstly, the distribution of normality for all the variables was checked by the Shapiro–Wilk test. Then, a descriptive analysis of baseline characteristics of the sample was reported, calculating the means and standard deviations for those variables with normal distribution and the median and interquartile range for those with non-normal distribution.

Subsequently, to assess the effects of the interventions, we conducted repeated measures analysis of variance (ANOVA) tests for quantitative variables (or Kruskal–Wallis test for non-normal variables) and the Bonferroni test as post hoc comparisons. Mixed-effect regression models considering the group effect, time effect, and group x time interaction were conducted. 

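### The pre/post group-by-time analysis does not condition on each participant's baseline value, so it is valid but less precise than an ANCOVA that uses data already collected

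*Protocol article*

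**What the plan says.** Section 2.4 fixes two measurement occasions: "All outcomes were evaluated before (2 min) and immediately after (2 min) the intervention". The baseline value of the primary outcome (conditioned pain modulation, CPM) and of the secondary outcomes (pressure pain thresholds, PPT, and temporal summation, TS) is therefore planned for every participant. The same section lists descriptors recorded beforehand, among them "age (years), gender (male or female), weight (kg), height (m" and "level of physical activity (measured by the short version of the International Physical Activity Questionnaire (IPAQ-SF".

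Section 2.8 sets the target as within-person change: "Changes in outcomes were tested on the basis of the intention-to-treat principle". It names repeated-measures ANOVA ("or Kruskal–Wallis test for non-normal variables") with Bonferroni post hoc comparisons, and then gives the model terms: "Mixed-effect regression models considering the group effect, time effect, and group x time interaction were conducted". Baseline appears as the first of two responses, not as a regressor, and no other covariate is named.

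Section 2.2 enrols "asymptomatic adults, aged 18 to 49 years, of both genders". Section 2.6 says "Concealed allocation was conducted with a computer-generated randomized table of numbers" and names no stratification factor.

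**The concern.** With one measurement before and one after, the group-by-time term compares mean changes between arms. That fixes the coefficient on baseline at 1. Unless pre and post values correlate perfectly, the best coefficient is smaller than 1, and fixing it at 1 adds noise to every between-group contrast.

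Precision matters here because the trial has little to spare. The sample size is set for a single two-group comparison at alpha 0.05, whereas the arms are to be compared with Bonferroni-corrected post hoc tests. A method that recovers precision from data already planned is worth having.

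**Working it through.** **1. The plan's own figure.** Inputs from Section 2.5: d = 1.05, alpha 0.05, power 80%. A two-sided two-sample t-test needs 15.26 per arm, rounded up to 16; power at 16 is 82.0%. Allowing 10% loss, 16/0.9 = 17.8, so 18 per arm and 4 × 18 = 72. The stated figures reproduce, for one uncorrected pair.

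**2. Variance of the two estimators.** Let the outcome have variance s² before and after, with correlation rho.
- Change score (what group × time estimates): 2s²(1 − rho).
- ANCOVA residual: s²(1 − rho²) = s²(1 − rho)(1 + rho).
- Ratio, ANCOVA to change score: (1 + rho)/2.

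The article gives no rho, so a range is assumed: at 0.8 the ratio is 0.90 (10% less variance) and at 0.5 it is 0.75 (25% less).

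**3. Power for one Bonferroni-corrected pair.** Assumptions: d = 1.05 in change-score SDs, 16 per arm, alpha = 0.05/6 for the six pairs among four arms, pooled error df = 4 × 16 − 4 = 60 (59 with a covariate), noncentral t. Noncentrality is d × √(16/2).

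| Analysis | Effective d | Noncentrality | Power |
|---|---|---|---|
| Stated group × time | 1.05 | 2.97 | 59.7% |
| ANCOVA, rho = 0.8 | 1.05/√0.90 = 1.11 | 3.13 | 65.5% |
| ANCOVA, rho = 0.5 | 1.05/√0.75 = 1.21 | 3.43 | 75.5% |

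If the covariate gained nothing, the lost degree of freedom would take power from 59.7% to 59.6%.

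**4. Check by simulation.** Four arms of 18, pre and post, random allocation, between-person SD 1, measurement SD 0.6, and a sex difference in level of 1. The implied rho is (1 + 0.25)/(1 + 0.25 + 0.36) = 0.78, so the formula predicts an SE ratio of √0.89 = 0.94. The mean SE was 0.284 for group × time and 0.269 for ANCOVA, a ratio of 0.95.

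**5. What sex adds.**
- In the stated model: in one data set with 6 against 12 men and a sex difference in level of 1, group × time was 0.0845 (SE 0.2833) both without and with a sex main effect. The level difference had already cancelled.
- In the ANCOVA, random allocation: when sex affected level only, adding it moved the mean SE from 0.269 to 0.267 (0.7%). When sex also altered the change by an assumed 0.4 (0.4/0.85 = 0.47 SD of change), it moved from 0.282 to 0.266 (about 6%).

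**The case against.** The strongest reply is that nothing in Section 2.8 is wrong. Group × time on randomised pre/post data is a valid and common analysis, and baseline is used, since it is the first response. The text lists effects that were considered without saying there were no others, and a journal article may leave covariates to a fuller document. Much of this stands. It makes the point an improvement and not an error. It does not remove the point, because the article spells out the model terms and the structure they describe is a comparison of changes.

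A reader might infer something stronger: that because sex, age and activity are collected but not modelled, chance sex imbalance in arms of 18 is left uncorrected. The imbalance itself is plausible. With an assumed 50% men and simple randomisation, two given arms differ by at least 4 men with probability 24%, and at least one of the six pairs does so in about 65% of trials. The consequence does not follow, for three reasons.
- Stable level differences cancel in the pre-post contrast, and a sex main effect added to the stated model changes nothing (step 5).
- Imbalance moves the contrast only if sex alters the change. The article gives no figure for that. At an assumed effect of 0.5 SD of change, a gap of 4 men in 18 shifts the contrast by 0.5 × 4/18 = 0.11 SD, against a design effect of 1.05.
- Under randomisation, chance imbalance is already covered by the stated error rate. Recording a descriptor creates no duty to adjust for it, and no stratification factor is named that the model would have to carry.

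One counterpoint concerns the fix. ANCOVA does not cancel a level difference completely when the arms happen to be unbalanced. In simulations with 6 against 12 men, a sex difference in level of 1 and no true effect, the mean estimate was 0.10 without sex in the ANCOVA and 0.01 with it. Averaged over randomisations there is no bias, but this is a fair reason to allow sex as a second covariate.

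The Kruskal–Wallis fallback has no time term. Run on post values, it would leave baseline differences in; run on changes, it would not. The article does not say which, so no firm conclusion can be drawn.

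**Conclusion.** The point holds as a matter of efficiency. The stated contrast is unbiased and valid, but it gives up 10% to 25% of its variance at an assumed rho of 0.8 to 0.5. The gain vanishes as rho approaches 1 and is larger below 0.5.

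The power figures (about 60% rising to about 66–75%) also rest on all six pairs being tested and on d = 1.05 being in change-score SDs. Section 2.5 ties that effect to the PPT change after the conditioning stimulus, which is not clearly the pre-to-post-intervention change in CPM. If d is instead in SDs of a single measurement, the change-scale effect is 1.05/√(2(1 − rho)). At rho = 0.5 this is again 1.05 and the figures are the same. At rho = 0.8 it is 1.66 and power is already about 97%, so little is left to gain. The variance ratio is the same on either scale.

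The shortfall to about 60% comes from the multiple comparisons, not from the missing covariate; baseline adjustment recovers part of it. The documents do not support a claim that the analysis is biased, or that omitting sex, age or activity is a defect. Importance is low.

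**What to change.** Make the primary between-group analysis of CPM, analysed as a quantitative score, an ANCOVA of the post-intervention value on group, with the baseline value of the same outcome as covariate. Analyse PPT (same site) and TS in the same way. A mixed model that constrains the baseline means to be equal across arms is an equivalent choice. Keep the stated group × time model as a sensitivity analysis.

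Sex may be pre-specified as an optional second covariate in the ANCOVA, with little gain to be expected. It should not be added as a main effect to the group × time model, where it does nothing. The covariates should be fixed before unblinding.

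Cost: one line of analysis wording and one or two of about 60 to 68 error degrees of freedom (4 × 16 − 4 to 4 × 18 − 4). No new data and no change to the sample size.

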## 3. Discussion

### 3.1. Potential Impact and Significance of the Study

This study hypothesizes that galvanic electrical current applied during percutaneous electrolysis is the responsible of the analgesia-induced produced by this intervention. With that hypothesis, we aim to determine if percutaneous electrolysis has a greater influence in the EPM than an isolated needling procedure or no intervention. Our second hypothesis was that there may be differences in activation of the EPM depending on the intensity and the time of application of percutaneous electrolysis. With that hypothesis, this study will include two different methodological applications (low intensity for a long period of time vs. high intensity for a short period of time) of galvanic electrical current. 

Previous studies have already explored the effects on EPM of different interventions, e.g., shock wave therapy [38], transcutaneous electrical nerve stimulation [39], manual therapy [40,41,42], or exercise [43,44,45]. Thus, this paradigm could potentially explain the analgesic effects of needling interventions, although no study has clarified this either [20]. In fact, EPM has been extensively studied with other treatment techniques resembling percutaneous electrolysis. For example, electroacupuncture also uses an electric current (biphasic wave -but not galvanic- current) through acupuncture needles, and its effects on pain have been related to an activation of descending pain inhibitory systems, but the results are conflicting [46]. In this context, it has been hypothesized that the results depend on the intensity of the electric current, since strong electroacupuncture is able to induce greater analgesic effects than weak electroacupuncture [47]. The effects on pain of other needling techniques, such as acupuncture or dry needling, have also been associated to EPM mechanisms [18,19,20]. Tobbackx et al. [33] conducted a clinical trial similar to the current one proposed here in which one session of acupuncture resulted in acute improvement in PPTs in the neck and calf, but had no effect on CPM or TS in patients with chronic whiplash-associated disorders.

To the best of the authors’ knowledge, there is no published article investigating the effects of percutaneous electrolysis on EPM. In fact, studies that have focused on changes in the nervous system after the application of this intervention found an increased parasympathetic activity, as measured by hearth-rate variability [1,2]. García-Bermejo et al. [1] added a group that received a needling procedure without the galvanic electrical current and found between-groups differences in favor of the application of electrical current throughout the needle. Similar results would be expected in the current study, with both needle and galvanic current influences and differences in favor of the use of an electrical current. Furthermore, we are not aware of any studies comparing the application of percutaneous electrolysis with high and low intensity of the electrical current, so we hope to provide some insight into this particular clinical practice issue.

### 3.2. Limitations

It should be recognized that this protocol has some limitations. First, this study will include healthy participants, which will make it difficult to extrapolate the results to daily clinical practice. Nevertheless, we consider that it is highly important to determine the physiological effects of an intervention such as percutaneous electrolysis first in healthy individuals showing proper CPM and as a second step to determine its effects in different chronic pain conditions, where CPM is usually impaired and, therefore, the response maybe different. Second, another consideration is the inclusion of a non-intervention group to determine the effects of time on CPM. Additionally, although the participants will be blinded from their group assignment, some subjects may perceive discomfort related to the application of galvanic current and identify the intervention that they receive. Successfully blinding will be confirmed by asking the participants which intervention they believed had received. It should be recognized that it will be not possible to blind the therapist who will apply the interventions, considering the treatment approach that is proposed. It would increase the risk of bias due to deviation from intended interventions. Finally, the results of this study will be restricted to the immediate effects of assessments. Since this is a mechanisms-related study, this is the common procedure in published studies [40,41,42].

### 3.3. Contributions to Physical Therapy

The lack of evidence concerning the mechanisms involved in pain reduction after the application of percutaneous electrolysis justifies the development of this randomized clinical trial. In fact, this study will be the first to investigate the influence of percutaneous electrolysis on EPM and its publication will represent a contribution in the field of the neurophysiological effects of needling techniques. In addition, this research may establish new research lines that will include subjects presenting with chronic pain conditions for observing possible differences with the results obtained in healthy subjects. This trial may also contribute to the development of application protocols based on different dosage of percutaneous electrolysis.

## Figures and Tables

**Figure 1 brainsci-11-00801-f001:**

Experimental protocol timeline. PPTs: pressure pain thresholds; CPM: conditioned pain modulation; TS: temporal summation; PE: percutaneous electrolysis.
